### Feasibility

According to the most recent laboratory urine sample submission (personal communication, 2012), an average of 364 urine samples (median 257, range 25 to 1,162) per year per eligible practice are sent in to the GUH laboratory. Considering that the intervention will run over a six-month period (Phases 2 and 3) and without any adjustment for the total number of UTI-related consultations, an estimated 3,640 urine samples will be submitted from 20 participating practices during this period. If 56% of these patients are prescribed an antimicrobial over a six-month period, a total of 2,038 patients will be prescribed an antimicrobial.

#### Secondary outcome: decrease in the quantity of consumption (control - intervention arm B)

To estimate the potential power to detect this secondary outcome, an additional sample size calculation was carried out.

• 56% of the patients presenting with a UTI, and for whom a urine sample was submitted for microbiological analysis, received a prescription
[8].

• A 20% decrease in consumption can be achieved through delayed prescribing
[42].

Taking account of the cluster effect and based on previous ICC estimates, a total sample size of 240 patients recruited from 20 practices gives a power of 80% to detect a significant change in the proportion of patients who reduce antimicrobial consumption through delayed prescribing if the ICC is 1%.

### Intervention

#### Overview of SIMPle intervention

The SIMPle intervention incorporates components that address GP and patient behaviours relating to antimicrobial prescribing and consumption. Each component is discussed individually. Table 
1 provides an overview of all intervention components.

**Table 1 T1:** Overview of SIMPle intervention components

**Intervention component**	**Study arm**	**Description**	**Primary objectives**	**Secondary objectives**
**GP focused**				
Coding workshop	All arms	Demonstrate the purpose of electronically coding UTI consultations using coding guidelines (International Classification of Primary Care code U71) and how to implement uniform coding in routine practice.	Promote routine uniform consultation coding for UTIs.	Gather baseline practice data and knowledge and attitudinal data (questionnaires).
Interactive workshop A	Intervention arm A	Raise the profile of GPs’ antimicrobial prescribing behaviours and their role in the broader issue of AMR.	Encourage GPs to become more aware of their antimicrobial prescribing behaviours through discussion of their role in the development of AMR.	Process evaluation
		Provide guidance on antimicrobial prescribing through adherence to guideline for UTI.		
Interactive workshop B	Intervention arm B	In addition to the core components of interactive workshop A, the recommendation to delay antimicrobial prescribing for UTIs facilitated through shared decision making will be promoted.		Encourage the use of delayed prescribing for UTIs.
				Process evaluation.
Electronic audit and feedback reports	Intervention arms A and B	A monthly report will be available (electronically) to practices summarizing their antimicrobial prescribing patterns for UTIs and antimicrobial resistance patterns of *E. coli*.	To provide a comparison of antimicrobial prescribing for UTIs between practices.	To provide an overview of antimicrobial resistance patterns in *E. coli* causing UTIs.
Stakeholder awareness		Information about the intervention and the issue of AMR will be provided to other stakeholders; pharmacists, practice receptionists and practice nurses.	To update all stakeholders on the overall aim of the intervention.	
Computer “prompt” application	Intervention arm A	Upon entry of the uniform UTI code, automated electronic prompts will appear on the GPs computer screen.	Provide the recommended antimicrobial treatment for a UTIs.	Remind the GP to collect urine samples and patients’ mobile telephone numbers.
	Intervention arm B		Provide the recommended antimicrobial treatment for a UTI and suggest delayed prescribing.	
**Patient focused components**				
Informational leaflets	Intervention arms A and B	Leaflets will outline the aim of the SIMPle study and highlight issues relating to consuming antibiotics. Intervention arm B patients will receive additional information, outlining the benefits of delayed prescribing for UTIs.	To increase awareness of the side effects, resistance and lack of the availability of new antibiotics.	To inform the patient of the study. To support the use of delayed prescribing for UTIs (patients in intervention group B only).
Educational infomercial		An educational video will be displayed in practice waiting rooms. The video will outline the key issues associated with AMR to patients.		
**GP and patient focused components**				
Website	Intervention arms A and B	The website will provide more information on the issues of AMR.	To provide access to an online survey.	Provide background to the SIMPle study.

### GP components

#### Intervention workshops

A coding workshop will be delivered to all practices at the beginning of Phase 1. Routine coding for UTIs using the International Classification of Primary Care code (U71: 'cystitis, urinary infection, other’) will be demonstrated. The advantage of routine coding of UTI consultations will be to facilitate the generation of electronic audit and feedback reports, which will be extracted through the iPCRN system (see further).

Contact information for GPs (for example, mobile telephone numbers, email addresses) will also be collected to facilitate reminders to code throughout the study period.

Phase 2 will begin with an interactive workshop for intervention arms A and B. The interactive workshops promote changes (where necessary) in antimicrobial prescribing for the treatment of UTIs by presenting an overview of prescribing and AMR, discussing the role of the GP in the spread of AMR and the potential positive impact of prescribing according to guidelines.

In addition, the interactive workshop delivered to practices in intervention arm B will support the GPs in recommending delaying antimicrobial treatment by 48 hours where appropriate. Based on the information provided in the workshop, the GP can discuss the benefits of delayed antimicrobial treatment for UTIs with the patient. This two-way communication will encourage patients to make an informed decision on their treatment. The decision to delay treatment will be shared between the GP and the patient.

The workshops will be delivered to each practice by members of the research team. General practitioners attending the workshops can receive continued professional development recognition for their participation from the Irish College of General Practitioners.

#### Computer prompt application

For intervention arms A and B, a computer prompt has been developed for use within the selected GP practice management software system. This prompt summarizes the recommendations for first-line antimicrobial treatment and will appear on the computer screen when the GP enters the International Classification of Primary Care code (U71) for 'cystitis, urinary infection, other’. In addition, for practices in intervention arm B, the prompt will include a recommendation to consider delayed antimicrobial prescribing. In intervention arms A and B this prompt will also remind the GP to collect patients’ mobile telephone numbers.

#### Electronic audit and feedback reports

Electronic audit and feedback reports will be available to download by GPs through the iPCRN. These reports will provide the practice with information on antimicrobial prescribing for UTI in comparison with the aggregated information from the other practices participating in the intervention. AMR patterns of bacteria causing UTIs will also be presented to the practice. The audit and feedback reports will be available to intervention arms A and B from the start of Phase 2, and to the control arm at the end of Phase 3.

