The use of audit and feedback of information in conjunction with other intervention methods (delayed prescribing, educational material or electronic prompts) has also proven effective in improving GPs antimicrobial prescribing behaviours
[2,36]. General practitioners in the UK receive routine feedback on their prescribing practices and are among the lowest community prescribers of antimicrobials in Europe
[30,37]. Currently, Irish GPs cannot readily access information on their prescribing practices, despite evidence to suggest that feedback can successfully reduce antimicrobial prescribing in the Irish primary care setting
[36].

The use of delayed antimicrobial prescribing for viral infections in primary care in the UK has been credited with achieving a 50% reduction in antimicrobial use
[22,38,39]. Empirical antimicrobial treatment for UTIs is currently recommended in the Guidelines for Antimicrobial Prescribing in Primary Care in Ireland
[11]. However, in at least 50% of patients with UTIs, an antimicrobial may not be required, as the infection resolves naturally
[40-42]. Qualitative studies investigating attitudes to delayed antimicrobial prescribing in primary care have indicated that both patients and GPs are satisfied with this treatment format and welcome this 'safety net’ approach as a feasible treatment strategy
[23,43-45].

Between the GP and patient, the communication of such treatment strategies as delayed prescribing can be viewed as part of a shared decision-making process
[23]. A shared decision-making process can empower patients through a greater understanding of the issues involved
[46,47]. Shared decision making with delayed prescribing allows patients to prioritize what they value most; increasing their chances of a quick recovery or reducing their chances of side effects and reconsultations in the future
[47,48].

The leading systematic review in the area of complex prescribing interventions in primary care called for innovative intervention methods to be developed
[2]. Around 75% of a general practice’s registered patients will wait in the practice waiting room each year and the demand for easy-to-understand healthcare information is increasing
[49]. The use of informative material in GPs waiting rooms, such as educational videos and interactive games, to create awareness and explain the problems associated with the overuse of antimicrobials in primary care, has also been recommended through the European Antibiotics Awareness Day

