#### Patient education

An infomercial (information commercial) explaining the two key messages (as previously outlined) has been developed for display in practice waiting rooms. An infomercial is a short video representation of information, data or knowledge intended to present complex information quickly and clearly. The infomercial will be displayed in an enclosed and fixed iPad in the practice waiting room. There will also be an option to play an AMR-themed game on this iPad, which will contain the same two messages as stated above. All intervention practices will be offered an iPad for their waiting room at the start of Phase 3 (Figure 
1). The impact of this component on antimicrobial prescribing and consumption will be evaluated in comparison with Phase 2. Both the infomercial and the game will be made freely available for download at the end of Phase 4.

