#### The control arm

To gather comparable data on UTI consultations, practices in the control arm will complete a coding workshop at the beginning of Phase 1. For the remainder of the intervention, the control arm will provide 'usual care’ and will receive their audit and feedback reports at the end of intervention Phase 3. Practices in the control arm will also submit urine samples from UTI patients and request patients’ mobile telephone numbers for the duration of the intervention.

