### Quantitative data collection

Data collection will involve five quantitative components: consultation data obtained through the iPCRN; questionnaire data from the GPs, along with a practice profile from the practice manager; Health Service Executive Primary Care Reimbursement Services (HSE-PCRS) prescribing data; and patient follow-up information through text messages. Data for the GPs will be collected at the beginning of Phase 1, immediately after the patient education intervention (Phase 3) and after a six-month follow-up (Phase 4). The collection of patient data will continue throughout Phases 2 and 3.

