### Quantitative data analysis

Data comparisons will be made between the start and end of the intervention. To assess sustainability, an additional comparison will be made six months after the end of the intervention. An overview of the data collected through the iPCRN, as outlined in data collection, will be presented for both practice and patient variables. Data will be presented and compared between each arm. Patients’ characteristics will be compared between the group who were followed up by text messaging and the group who did not participate in text messaging.

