### Method of quantitative data analysis

Quantitative analysis will be undertaken using SPSS for Windows release 20.0 (SPSS Inc., Chicago, IL, USA) and Stata 11 (Stata Corporation, Texas). Multilevel analysis will be performed using MLwiN version 2.21 software and cost-effectiveness analysis will be conducted using Excel and Stata 11. Statistical significance will be set at the 5% level for all outcomes.

Multivariate analysis will examine intervention and control arm changes from baseline measures and will follow the principle of intention to treat. Outcomes will be compared between intervention (arms A and B) and the control arm, using a multilevel logistic modelling approach to control for baseline prescribing as well as other confounding variables at patient and practice level. All statistical analysis will be undertaken in accordance with current guidelines for randomized controlled trials
[71].

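### Control practices get audit and feedback reports at the end of Phase 3, so the six-month sustainability comparison has no control free of intervention components

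*Protocol article*

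**What the plan says.** Table 1 of the protocol article lists electronic audit and feedback reports as a component for intervention arms A and B, produced monthly. The section on electronic audit and feedback reports makes them available to those arms from the start of Phase 2 "and to the control arm at the end of Phase 3". The section on the control arm repeats this timing: those practices provide usual care and "will receive their audit and feedback reports at the end of intervention Phase 3".

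Under quantitative data analysis, the article adds a later time point: "To assess sustainability, an additional comparison will be made six months after the end of the intervention". The same paragraph states "Data will be presented and compared between each arm", and the methods of quantitative analysis say "Outcomes will be compared between intervention (arms A and B) and the control arm". The data collection section places a GP data point "after a six-month follow-up (Phase 4").

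The limitations section names the coding workshop as an influence on the control arm. It does not mention the release of feedback reports to that arm.

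**The concern.** A sustainability comparison asks whether the difference produced by the intervention is still there after it stops. To answer that against a randomised control, the control arm must stay free of the intervention until the comparison is made. Here the control arm is offered one of the components just as the follow-up period begins.

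The article gives reason to think the component is active. Its background section cites evidence that "feedback can successfully reduce antimicrobial prescribing in the Irish primary care setting" and says that Irish GPs cannot otherwise readily see such information. The reports also set a practice's UTI prescribing beside the aggregate of the other participating practices.

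If some control practices move towards first-line prescribing in response, the difference between arms shrinks even if arms A and B hold their gains. The likely error is towards concluding that the effect was not sustained. This matters for a study that presents sustainability beyond the intervention period as one of its aims.

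**Working it through.** **Timeline.** Setting the sections side by side:

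| Period | Arms A and B | Control |
|---|---|---|
| Phase 1 | Coding workshop | Coding workshop |
| Phases 2 and 3 (six months) | Interactive workshop, prompts, feedback reports, patient materials | Usual care |
| End of Phase 3 | End-of-intervention comparison | Feedback reports released |
| Six months later (Phase 4) | Sustainability comparison | Sustainability comparison, reports already available |

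The release comes at the end of the period used for the primary comparison and before the sustainability comparison. Only the latter is exposed.

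**Is there a stated figure to reproduce?** None for the sustainability comparison. The nearest is the primary sample size for control against arm A: 920 patients in 20 practices, 80% power, alpha 5%, ICC 1%, 38% rising by 10 points to 48%. I used it to check the method.

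- Cluster size m = 920/20 = 46. Design effect = 1 + (46 − 1) × 0.01 = 1.45. Effective n per arm = 460/1.45 = 317.2.
- Power = Φ{[d − z√(2p̄(1 − p̄)/n)] / √([p1(1 − p1) + p2(1 − p2)]/n)}, where d = p2 − p1, p̄ is the mean of p1 and p2, and n is the effective size per arm.
- Result: 82% with one-sided 5% (z = 1.645) and 72% with two-sided 5% (z = 1.96). The article does not state sidedness. The method comes within two points of the stated 80% on the one-sided reading. I use two-sided 5% below.

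**Illustration for the six-month comparison.** Assumptions that the article does not supply:

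- arm A holds at 48%;
- control rises from 38% by 0, 2, 3 or 5 points;
- Phase 4 yields the same 2,038 antimicrobial prescriptions that the feasibility section estimates for the six intervention months in 20 practices;
- practices are equal in size.

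m = 2,038/20 = 101.9. Design effect = 1 + 100.9 × 0.01 = 2.009. Effective n per arm = 1,019/2.009 = 507.2.

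- No rise (0.38 v 0.48): (0.10 − 1.96 × 0.03109)/0.03093 = 1.263, power 90%.
- Rise of 3 points (0.41 v 0.48): (0.07 − 1.96 × 0.03121)/0.03113 = 0.284, power 61%.
- Rise of 5 points (0.43 v 0.48): (0.05 − 1.96 × 0.03127)/0.03123 = −0.361, power 36%.

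| Assumed control rise | Gap left | Power, 2,038 patients | Power, 920 patients |
|---|---|---|---|
| 0 points | 10 points | 90% | 72% |
| 2 points | 8 points | 73% | 53% |
| 3 points | 7 points | 61% | 43% |
| 5 points | 5 points | 36% | 24% |

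The loss of power is secondary. The estimated gap itself falls one for one with any control rise, and a larger sample does not correct that.

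**The case against.** The case on the other side has several parts.

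- **Reach.** Sustainability is an additional comparison. It is not among the listed objectives and has no power claim. A reader might infer that the trial's main result is compromised. The article does not support that, because controls stay on usual care until the end of Phase 3. This stands and limits the point.
- **Extent of exposure.** A reader might infer full contamination of every control practice for all six months. The article does not support that either. Reports are only available to download, the text does not say whether controls get one report or continuing access, and controls receive neither the interactive workshop nor the prompts. This stands: it is possible partial exposure to one component.
- **Strength of the evidence on feedback.** The background section supports audit and feedback mainly in combination with other methods, and its Irish evidence concerns reduced prescribing, not the share that is first-line. This stands, and it is why the control rise above is only an assumption.
- **Other information.** Monthly first-line rates by arm are planned, the number of audits generated is recorded for each practice, and regional reimbursement data are compared. If the monthly rates run into Phase 4, a fall in A or B and a rise in control could each be seen. This helps interpretation but does not replace an unexposed randomised control.
- **Type of comparison.** The sustainability sentence follows one about start and end of the intervention, so it could mean change within arms. The article also says patient data are collected throughout Phases 2 and 3, which leaves the Phase 4 content unclear. A between-arm reading is plausible from the general statements on comparing arms, but is not explicit for this time point. On the within-arm reading there is still no unexposed concurrent control.

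The infomercial and game are released for download only later ("Both the infomercial and the game will be made freely available for download at the end of Phase 4"). One might infer that this was done to protect the control arm, but the article gives no such reason. It shows only that a later release date is workable.

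**Conclusion.** The point holds for the six-month sustainability comparison alone. As scheduled, that comparison has no control free of intervention components. A narrower gap could reflect waning in A or B, improvement in control, or both, and no later analysis can restore the missing contrast. The bias, if present, runs towards finding no sustained effect.

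Its size cannot be derived from the article. On the assumed control rise of 3 to 5 points, a maintained 10-point difference would appear as 7 to 5 points, and power would fall from about 90% to between about 61% and 36%. These figures rest on that rise, on the intervention-period volume carrying over to Phase 4, on equal practices and on a two-sided 5% test. They show scale and are not a forecast. This should be corrected because the remedy is simple, but it does not threaten the primary result.

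**What to change.** Amend the sections on electronic audit and feedback reports and on the control arm so that control practices receive their reports only after the six-month Phase 4 data have been extracted. The cost is a change of wording, a note to the control practices and a wait of about six months for their reports.

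Thirty practices are already recruited and the invitation described benefits of taking part, so the reports may already have been promised for the end of Phase 3; the article does not say. If so, keep the schedule but make the end of Phase 3 the last randomised comparison. Report the six-month data as description within each arm, alongside control-arm use of the reports, taken from the audit counts already listed under consultation data. The cost is giving up a randomised statement about sustainability.

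Under either option, state whether control access is a single report or continuing, and add this exposure to the limitations section.

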#### Stakeholder awareness

All relevant gatekeepers who are directly or indirectly involved in the implementation of the intervention will receive information on the SIMPle study. These gatekeepers include practice staff, such as the receptionist, practice managers and nurses. Local pharmacists will also be informed of the intervention prior to its launch. The use of delayed antimicrobial prescribing for UTIs will be communicated to local pharmacists to provide support in the event of a patient requiring further information.

#### Patient components

The key messages about antimicrobials underlying the design of all patient focused materials are:

1. Taking an antimicrobial for an infection now increases your chances of having a resistant bacterial infection in the future.

2. Owing to the development of AMR, we are running out of antimicrobial treatment options for more serious bacterial infections.

